### Reproductive Outcomes

The primary outcome is MII oocytes rate (percentage of the number of mature oocytes to the number of oocytes retrieved).

The secondary outcomes are number of oocytes retrieved, fertilization rate (the proportion of oocytes that become fertilized), top quality embryos (TQE) rate (percentage of the number of TQE to total embryos obtained), blastula formation rate, embryo implantation rate (percentage of the number of gestational sac to the total transferred embryos), clinical pregnancy rate (percentage of participants with clinical pregnancy), miscarriage rate (percentage of participants with loss of a diagnosed clinical pregnancy before 12 weeks gestation), live birth rate (the proportion of a delivery of one or more living infants), cumulative pregnancy/live birth rates (percentage of participants with clinical pregnancy/live birth after one year of follow-up), severe OHSS rate (percentage of participants with OHSS). TQE was defined as seven or more blastomeres on day three, evenly sized blastomeres, and less than 20% fragmentation, whereas low quality embryos were characterized as anything else. On transvaginal ultrasonography, clinical pregnancy was defined as the appearance of a gestational sac and foetal heartbeat.

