### Sample Size Estimation

This clinical study is a superiority, randomized parallel controlled trial. GnRH-a+hCG (dual trigger) in group A and hCG-only trigger in group B. MII oocytes rate will be the primary outcome measurement. According to previous data of our centre, the estimated rate of MII oocytes in group B was **40%**, and **70%** in group A after using GnRH-a (40h before OPU) + hCG (34h before OPU) dual trigger, with **standard deviations of 40%** for each group. Suppose that α=0.05 (two-sided) and β=0.10 (90% power), the sample size is calculated to be 40 individuals for each group by PASS 15.0 (NCSS, LLC. Kaysville, Utah, USA.). Assuming a dropout rate of 10%, the sample size 45 individuals for each group will be required. Ultimately, a total of 90 individuals will be recruited for this study.

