### Data Statistical Analysis

All randomized individuals will be included in the analysis of the primary trial end point (intention-to-treat analysis). For analyses of other outcome variables, only subjects randomized to the study protocol will be included (per-protocol analysis). SPSS version 26.0 and R statistical package version 4.0.0 will be used to analyse all the data. The continuous data will be normalized using the two independent samples t-test and presented as mean ± standard deviation (Mean ± SD). If the distribution is not normal, use nonparametric tests, which are expressed as the median (interquartile range) [M (IQR)]. Categorical data will be presented as frequency (percentage) [n (%)] using chi square test and Fisher’s exact test for expected frequencies less than five. P < 0.05 indicates that the difference is statistically significant.

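### Fertilization, top-quality embryo and implantation rates are counted over oocytes or embryos, but no named test allows for clustering within the randomised woman

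*Protocol article*

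**What the plan says.** **Outcome definitions (Protocol article, Reproductive Outcomes).** Two kinds of denominator appear in one list. Clinical pregnancy, miscarriage, cumulative pregnancy and live birth, and OHSS are percentages of participants. Fertilization is a proportion of oocytes, the top-quality embryo rate is taken over all embryos obtained, and the implantation rate is the "percentage of the number of gestational sac to the total transferred embryos". Blastula formation rate is listed without a definition. The primary MII rate is the "percentage of the number of mature oocytes to the number of oocytes retrieved". None of the oocyte or embryo ratios is said to be calculated per woman or pooled over the arm.

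**Sample size (Sample Size Estimation).** The MII rate is sized from "the estimated rate of MII oocytes in group B was 40%, and 70% in group A", "with standard deviations of 40% for each group", and the result is counted in individuals: 40 per arm, 45 after allowing for 10% dropout.

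**Tests (Data Statistical Analysis).** There are two generic rules. Continuous data go to a two-sample t-test, or to a nonparametric test if not normal. For the rest: "Categorical data will be presented as frequency (percentage) [n (%)] using chi square test", with Fisher's exact test when expected frequencies are below five. No outcome is assigned by name to either rule, and within-woman correlation is not mentioned.

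**The concern.** The woman is randomised, and her oocytes and embryos share her biology and her cycle. In this trial each woman is enrolled because at least half of her own oocytes were immature in a previous cycle, so correlation within women is to be expected.

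A chi-square or Fisher test on pooled counts treats every oocyte or embryo as independent. With positive correlation within women its standard error is too small, and it rejects a true null hypothesis more often than 5% of the time. Because the outcome list uses participants as the denominator for some outcomes and oocytes or embryos for others, a natural reading is that the latter are pooled, shown as counts with percentages, and tested by chi-square.

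At stake are mainly the secondary claims on fertilization, embryo quality and implantation. For the primary outcome the issue is that the test must be inferred from the sample-size section, when one sentence could state it.

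**Working it through.** **1. Which analysis does the sample size assume?** Inputs from Sample Size Estimation: 40% v 70%, SD 40%, two-sided α = 0.05, power 90%.

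- Comparison of per-woman means: n = 2(1.960 + 1.282)² × 0.40² / 0.30² = 37.4, so 38 per arm. The noncentral t gives 39, and power at 40 per arm is 91.2%. This agrees with the stated 40 to within two women.
- Comparison of two independent proportions, 0.40 v 0.70: 56 per arm (63 with continuity correction). This does not give 40.
- Dropout: 40 / 0.90 = 44.4, so 45 per arm, as stated.

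The trial was therefore sized on one MII proportion per woman.

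**2. Formula for the pooled test.** With m units per woman, the design effect is DE = 1 + (m − 1) × ICC. A nominal 5% unadjusted chi-square then has type I error of about 2[1 − Φ(1.96/√DE)].

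**3. Implantation rate.** The article (Patient and Public Involvement) mentions transfer of one or two embryos. With m = 2, DE = 1 + ICC. The ICC is not given, so a range is assumed.

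| Assumed ICC | DE | Type I error |
|---|---|---|
| 0.1 | 1.1 | 6.2% |
| 0.2 | 1.2 | 7.4% |
| 0.5 | 1.5 | 11.0% |
| 1 (upper limit) | 2.0 | 16.6% |

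If some women receive only one embryo, the inflation is smaller. The upper limit assumes that no woman contributes more than two embryos.

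**4. Top-quality embryo rate.** Neither embryos per woman nor the ICC is given. Assume m = 5.

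- ICC 0.1: DE = 1 + 4 × 0.1 = 1.4, type I error about 10%.
- ICC 0.2: DE = 1 + 4 × 0.2 = 1.8, type I error about 14%.

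Fertilization has oocyte denominators, so the direction is the same. The article gives no SD or ICC for it, and no separate figure is offered here.

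**5. MII rate, only if it were pooled.** Here the SD is given. The variance of a woman's proportion is p(1 − p) × DE / m. Setting this to 0.40² gives DE = 0.16m / [p(1 − p)]. At p = 0.40, p(1 − p) = 0.24. Oocytes per woman are not given; 6 to 15 is an assumption borrowed from the antral follicle count entry range, which is not an oocyte count.

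| Assumed m | DE | Implied ICC | Type I error, formula | Type I error, simulation |
|---|---|---|---|---|
| 6 | 0.96/0.24 = 4.0 | 0.60 | 32.7% | 33.0% |
| 10 | 1.60/0.24 = 6.7 | 0.63 | 44.8% | 45.3% |
| 15 | 2.40/0.24 = 10.0 | 0.64 | 53.5% | 53.6% |

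The simulation used beta-binomial data, 45 women per arm, no true effect and 20,000 runs per row. A per-woman t-test on the same data rejected in 4.9-5.3% of runs. At p = 0.70 the formula gives 35.9% (m = 6) to 56.2% (m = 15).

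**The case against.** The strongest defence is that the article never sends an oocyte or embryo rate to chi-square. Its two rules are generic. For the primary outcome the sample-size section indicates which one applies: a mean, an SD and a count of individuals describe a continuous value per woman, and the t-test or nonparametric route holds about 5%. This stands. A reader might infer that the primary analysis is planned as a pooled chi-square with a one-in-three to one-in-two false-positive rate. The documents do not support that, because the stated 40 per arm is reproduced only as a comparison of per-woman means.

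A reader might also carry the 33-54% over to the embryo outcomes. That is not supported either. The 40% SD is given for the MII rate alone, embryo denominators are smaller, and implantation with at most two embryos per woman cannot exceed about 17%.

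It can further be said that the choice of a clustered model belongs in an analysis plan that is not shown. That is fair as to the model. But the article does state tests, and the only one it states for counts and percentages is invalid for pooled oocytes or embryos. The sample-size argument that protects the MII rate is not available for the secondary rates, and the implantation definition in particular leans towards pooling.

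**Conclusion.** The point holds as a cheap improvement, not as a failure of the primary analysis. The unit of analysis for the oocyte and embryo rates is not fixed, and the only test named for counts with percentages ignores clustering within women.

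If the secondary rates are pooled and tested that way, type I error is above 5% whenever the ICC is positive. The illustrative sizes, about 6-11% for implantation and 10-14% for the top-quality embryo rate, rest on assumed ICCs and, for the latter, an assumed embryo count. The 33-54% describes only a pooled MII rate at the stated 40% SD and an assumed 6-15 oocytes per woman. It shows why the per-woman analysis should be written down and does not predict what the trial will do.

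**What to change.** In Data Statistical Analysis:

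- State that the woman is the unit of analysis for all outcomes.
- Assign the MII rate by name to the continuous-data rule, as one proportion per woman, matching the sample size.
- Analyse fertilization, top-quality embryo, blastula formation and implantation rates with a method that allows for clustering by woman, for example logistic GEE with robust standard errors, or as per-woman proportions.
- Restrict chi-square and Fisher's exact test to outcomes counted once per woman, such as clinical pregnancy, miscarriage, live birth and OHSS.

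The cost is a few sentences and a few lines of code in R, which the article already names. Sample size and conduct do not change. The downside is wider confidence intervals for the secondary rates than a pooled test would show.

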### Adverse Events and Data Safety and Monitoring

An independent data safety and monitoring committee will be established to monitor the occurrence of adverse events. During the trial, the principal investigator will be followed up by telephone at any time and subjects will provide details if any adverse events arise. Participants will also be interviewed on the day of oocyte retrieval to determine if any adverse events occur serious adverse events will be recorded separately and will be followed up until resolution.

### Concomitant Care

Standard concomitant treatments such as folic acid supplements will be allowed in addition to the trial protocols and inclusion/exclusion criteria listed above.

### Patient and Public Involvement

Women and their partners beginning ART therapy at the reproductive centre of integrative medicine, the affiliated hospital of Shandong University of Traditional Chinese Medicine, will be included in the study. We asked about their experience of assisted conception, the things they liked and disliked, and the potential difficulties or barriers to attending for treatment, which may affect randomization. Participant requirements for the transfer of one or two embryos may have influenced part of the results. All elements of this study (creation of the study topic, study design and study conduct, interpretation of findings, and final manuscript editing for publication) are conducted without the participation of patients or the general public. The findings will be allowed to share with participants by their physicians.

### Ethics and Dissemination

The study was approved by the reproductive ethics committee of the Affiliated Hospital of Shandong University of Traditional Chinese Medicine (Identifier: SDUTCM/2021.7.26). Any modifications to the protocol that may affect the management, design, conduct, or safety of the study require a formal amendment to the Committee. COH followed by pharmaceutical trigger will be performed according to the routine IVF procedure. Safety was considered high for trial participants. All participants will provide written informed consent. No additional financial costs were required for study participants other than transportation. The results of this study will be disseminated in a peer-reviewed scientific journal.

## Discussion

In IVF/ICSI technology, the use of a pharmaceutical trigger to drive the final maturation of the oocyte is a crucial step. The LH effect produced by natural cycle lasts for 48 hours. As a common pharmaceutical used as trigger, hCG plays a role in promoting the final maturation of oocytes instead of endogenous LH. But the effect of 10, 000 IU hCG is 20 times greater than that of endogenous LH and can last more than 120 hours (1). Although the effects of hCG are long-lasting and can promote the production of corpus luteum in favour of embryo implantation and ongoing pregnancy. But it is precisely because of its strong and sustained action that leads to an increased risk of OHSS during the hCG trigger cycle. GnRH-a trigger has the advantage of driving the production of endogenous LH and FSH. LH and FSH act synergistically to promote oocyte final maturation and ovulation, which seems to be more favourable for oocyte quality. However, due to the effects of GnRH-a last only 24-36 h, leading to subsequent luteal insufficiency, they adversely affect pregnancy outcomes and live birth rates. Thus GnRH-a trigger still has certain limitations in the clinic.

The use of GnRH-a and a standard dose of hCG at 40 and 34 hours prior to oocyte retrieval was previously found to produce an elevated proportion of low mature oocytes compared to previous hCG trigger cycles and to successfully obtain mature oocytes in a patient with EFS. This study is a prospective, randomized, superiority-controlled trial to investigate whether dual trigger could improve reproductive outcomes in people with NOR, with the aim of identifying a more optimal trigger method. If this trigger method does improve IVF/ICSI outcomes, it may become a routine trigger method to boon more infertile couples. The subsequent results of this study, which may provide some data support for our next randomized controlled trial.

## Ethics Statement

The reproductive ethics committee of the Affiliated Hospital of Shandong University of Traditional Chinese Medicine certified this study (Identifier: SDUTCM/2021.7.26). The patients/participants provided their written informed consent to participate in this study.

